## Abstract

**Background:**

The global prevalence of chronic hepatitis B is more than 300 million people, and in Denmark, 17,000 people are estimated to have chronic hepatitis B. Untreated, chronic hepatitis B can lead to the development of liver cirrhosis and liver cancer. There is no curable therapy. In persons with obesity and chronic hepatitis B infection, the development of hepatic steatosis imposes a double burden on the liver, leading to an increased risk of cirrhosis and liver cancer. In patients without chronic hepatitis B, exercise interventions have shown beneficial effects on hepatic steatosis through improvements in fat fraction of the liver, insulin resistance, fatty acid metabolism, and glucose metabolism, as well as activation of liver-induced regulatory protein secretion (hepatokines) after the exercise intervention.

**Objective:**

To investigate in persons with chronic hepatitis B and hepatic steatosis:Primary: Whether exercise will decrease the fat fraction of the liver.Secondary: If exercise will affect hepatokine secretion and if it will improve lipid- and glucose metabolism, liver status, markers of inflammation, body composition, and blood pressure.

**Methods:**

A randomized, controlled, clinical intervention trial consisting of 12 weeks of aerobic exercise training or no intervention. Thirty persons with chronic hepatitis B and hepatic steatosis will be randomized 1:1. Before and after the intervention, participants will undergo an MRI scan of the liver, blood sampling, oral glucose tolerance test, fibroscan, VO2_max_ test, DXA scan, blood pressure measurements, and optional liver biopsy. Lastly, a hormone infusion test with somatostatin and glucagon to increase the glucagon/insulin ratio for stimulating secretion of circulating hepatokines will be performed. The training program includes three weekly training sessions of 40 min/session over 12 weeks.

**Discussion:**

This trial, investigating high-intensity interval training in persons with chronic hepatitis B and hepatic steatosis, is the first exercise intervention trial performed on this group of patients. If exercise reduces hepatic steatosis and induces other beneficial effects of clinical markers in this group of patients, there might be an indication to recommend exercise as part of treatment. Furthermore, the investigation of the effect of exercise on hepatokine secretion will provide more knowledge on the effects of exercise on the liver.

**Trial registration:**

Danish Capital Regions committee on health research ethics reference: H-21034236 (version 1.4 date: 19–07-2022) and ClinicalTrials.gov: NCT05265026.

## Introduction

### Background and rationale {6a}

Hepatitis B virus (HBV) causes chronic hepatitis B (CHB), which is defined as hepatitis B surface antigen (HBsAg) in the blood > 6 months. The estimated global prevalence of CHB is estimated to be 316 million individuals [1], and CHB is the most common type of hepatitis in the world. Untreated, CHB can lead to the development of liver cirrhosis and cancer, known as hepatocellular carcinoma (HCC). There is at present no curable therapy, but medical treatment can reduce the amount of virus in the blood, leading to reduced CHB-induced morbidity and mortality.

#### Comorbidity in persons with CHB

Persons with CHB have a higher body mass index (BMI), consume more alcohol, and have poorer physical fitness compared to uninfected [2], and approximately 33% are overweight and 50% physically inactive [3]. In general, especially central obesity is associated with the metabolic syndrome (i.e. central obesity, hypertension, glucose abnormality, and dyslipidemia) and thereby increased risk of development metabolic diseases such as type 2 diabetes (T2DM) and cardiovascular disease (CVD) [4]. Metabolic dysfunction is associated with non-alcoholic fatty liver disease (NAFLD) [5, 6]. NAFLD is projected to have a prevalence of > 30% in Asia and the USA populations [7, 8]. NAFLD is defined by the presence of steatosis > 5% in the hepatocytes [9] but excludes the diagnosis of hepatitis B. Hence, this trial will refer to the term hepatic steatosis when describing fatty liver disease in persons with CHB. The prevalence of concomitant hepatic steatosis and CHB vary dependent on degree of obesity, hypertriglyceridemia, and T2DM [10, 11]. In a meta-analysis including 21 studies comprising 4100 persons with CHB, the prevalence of biopsy-proven hepatic steatosis was 29.6% [12]. Other studies have indicated a prevalence of 14–30% [13], and a recent meta-analysis including 98 studies using a variety of ultrasound, liver biopsies, controlled attenuated parameter and magnetic resonance spectroscopy, to assess hepatic steatosis in persons with CHB, a prevalence of 35% was reported [14]. In persons with obesity and CHB, the development of hepatic steatosis imposes a double burden on the liver. Having CHB and hepatic steatosis have been shown to increase the risk of cirrhosis and HCC [15, 16].

#### Systemic inflammation in persons with CHB and comorbidity

Obesity is associated with chronic systemic low-grade inflammation, which is the key point in the initiation and progression of obesity-related NAFLD [17–19]. Chronic systemic low-grade inflammation is characterized by a two- to fourfold elevation in circulating levels of inflammatory cytokines and acute-phase reactants [20]. One of the main mechanisms is thought to be increased inflammation of the adipose tissue [21]. Circulating levels of tumor necrosis factor (TNF)-alpha and interleukin (IL)-6 are increased in chronic HBV infection and are positively associated with disease progression (hepatitis B progression to cirrhosis or HCC) [22, 23]. Whether chronic inflammation is due to HBV infection, comorbidities like obesity and T2DM, or both is unclear [24].

#### Hepatokines in persons with CHB

Another unclear mechanism is the signalling pathways of hepatokines. Hepatokines are proteins secreted by hepatocytes, and several hepatokines have been associated with metabolic dysfunctions [25, 26]. Hepatokines are suggested to change during HBV infection. Increased plasma levels of the hepatokine Fibroblast Growth Factor 21 (FGF-21) are associated with hepatic steatosis [27], but low levels of FGF-21 are associated with advanced fibrosis/cirrhosis in patients with CHB. FGF-21 is regulated by glucagon as well as macronutrients and is increased after exercise [28]. Another hepatokine, follistatin, plays a critical role in hepatocyte regeneration during the repair of liver tissue [29] and is also a part of the process of muscle hypertrophy [30]. Follistatin has an inverse correlation with HBV DNA levels [31]. The hepatokine angiopoeitin like protein 4 (ANGPTL4) and growth differentiation factor-15 (GDF-15) is secreted from the liver during exercise [32, 33] and ANGPTL4 is involved in regulating plasma triglyceride levels [34]. In patients with HBV-associated HCC GDF-15 is found to be increased and have an association with alpha-fetoprotein [35]. No studies have yet explored ANGPTL4’s relation to CHB. Studies investigating the secretion of the hepatokines are warranted to understand how the pathways are regulated and which target areas future medical treatment should focus on.

#### Effects of exercise

Exercise interventions of 6 weeks or more show beneficial effects on NAFLD patients without CHB through improvements in the fat fraction of the liver [36, 37], liver and peripheral insulin resistance, liver fatty acid metabolism and activation of anti-inflammatory cascades after the physical exercise intervention [38]. The anti-inflammatory properties of exercise are multifactorial. At least due to both a reduction in visceral adipose tissue and a more direct induction of anti-inflammatory, immune cells.

IL-6 is a cytokine implicated in the regulation of energy metabolism [39, 40]. IL-6 can be persistently elevated in individuals with obesity [41] and acutely following infection [42] and exercise [43, 44]. In exercise settings, IL-6 is not preceded by an increase in plasma TNF-alpha as seen during infections. During exercise, IL-6 is produced by contracting muscle fibers and released as a myokine into the bloodstream [44, 45]. It has been suggested that IL-6 could suppress HBV replication and inhibit HBV entry [45, 46]. The possible beneficial effect of the exercise-induced increase in circulating IL-6 in chronic HBV infection is unknown.

It is important to clarify the role of aerobic exercise training in preventing developing comorbidity and treating lifestyle-induced conditions like obesity, glucose tolerance, and fatty liver disease. Furthermore, it is necessary to understand the metabolic mechanism of activating inflammatory cascades and signalling through cytokines and hepatokines to improve targeting treatment of the double burden of chronically diseased persons. To our knowledge, no randomized exercise intervention trial has ever been made in persons with CHB. We wish to conduct a randomized controlled intervention trial to investigate the effects of aerobic exercise training on persons with CHB and hepatic steatosis to investigate the changes in the fat fraction of the liver and how aerobic exercise training alternates conditions related to the metabolic syndrome and cytokine and hepatokine secretion.

### Objectives {7}

The main objective is to investigate if regular aerobic exercise training can decrease the amount of fat in the liver in persons with CHB and hepatic steatosis.

A secondary objective is to investigate the effects of aerobic exercise training on hepatokine secretion in persons with CHB and hepatic steatosis. We also aim to investigate if regular aerobic exercise training will reduce obesity and improve lipid and glucose metabolism, liver status—such as elevated ALT and INR, markers of inflammation, body composition, and blood pressure in persons with CHB and hepatic steatosis.

#### Hypothesis

##### Primary hypothesis

Regular aerobic exercise training decreases the fat fraction of the liver.

##### Secondary hypothesis

Exercise-induced hepatokine release, glucose, and lipid metabolism are compromised in persons with CHB and hepatic steatosis and benefit from aerobic exercise training.

### Trial design {8}

This is an investigator-initiated trial that was registered at www.ClinicalTrials.gov before inclusion of the first participant. The trial is designed as a block-randomized, controlled, unblinded, clinical, superiority, exploratory, intervention trial. Thirty persons with CHB and hepatic steatosis are randomized 1:1 to either aerobic exercise training (intervention group, *n* = 15) or no intervention (“do-as-usual” control group, *n* = 15). See Fig. 1 for the study design. The trial will be reported using the CONSORT extension for non-pharmacological treatment interventions [47] and key elements from the REPORT Trial guide [48].

**Fig. 1 Fig1:**
[figure not shown]
Study design

## Methods: participants, intervention, and outcomes

### Study setting {9}

The trial visits will take place at the Centre for Physical Activity Research (CFAS), Copenhagen University Hospital, Rigshospitalet with magnetic resonance imaging (MRI) examinations at the Department of Radiology at Copenhagen University Hospital, Rigshospitalet. The liver biopsy (not mandatory) and the fibroscans will be performed at the Department of Infectious Diseases, Copenhagen University Hospital, Hvidovre. The aerobic exercise training sessions will be carried out at CFAS, or at the Department of Physio- and Occupational Therapy at Copenhagen University Hospital, Hvidovre.

### Eligibility criteria {10}

Trial participants will be recruited at three departments in Copenhagen University Hospital Denmark at a regular outpatient visit: the Department of Infectious Diseases, Copenhagen University Hospital, Hvidovre, the Department of Infectious Diseases, Copenhagen University Hospital, Rigshospitalet, and the Department of Internal Medicine, Copenhagen University Hospital, Herlev; all departments are part of hospitals in the Copenhagen metropolitan area in Denmark. Recruitment posters will be posted online, and participants will be able to contact the principal investigator if interested. See Fig. 2 for flowchart.

**Fig. 2 Fig2:**
[figure not shown]
Flowchart of participants

#### Criteria of inclusion

CHB defined by HBsAg positive > 6 monthsPositive Hepatitis B virus-DNAAge ≥ 30 years (no upper age limit)Hepatic steatosis diagnosed by controlled attenuated parameter (CAP) > 250 assessed by transient elastography or by ultrasound-defined hepatic steatosis

#### Criteria of exclusion

Human immunodeficiency virus (HIV), hepatitis C virus (HCV), or hepatitis D virus (HDV) co-infectionPrimary biliary cholangitisWilson’s diseaseAutoimmune hepatitisHepatocellular carcinomaAntiviral medicationSteatogenic medication (systemic corticosteroids, amiodarone, tamoxifen, valproic acid, and methotrexate)Contraindications for MRI scanAverage daily alcohol intake > 30 g for men and > 20 g for womenCoronary artery disease contraindicating HIITUnable to understand and read written information for participant’s written consentPregnancy

Since the liver biopsy is optional, participants with contraindications for a liver biopsy, can be included in the study without having a liver biopsy performed.

### Who will take informed consent? {26a}

The primary investigator or a project nurse will take the informed consent.

### Additional consent provisions for collection and use of participant data and biological specimens {26b}

On the consent form, it is stated in a separate paragraph that participants give consent to the collection of blood plasma to be stored in a research biobank. The biobank is under the legal supervision of the Danish Data Protection Regulation. Any future research using the plasma will be approved by the Danish Capital Regions Committee on health research ethics and, if required by the committee, the participants will give their consent again for a specific project.

## Interventions

### Explanation for the choice of comparators {6b}

We choose to do a randomized controlled clinical trial involving persons with CHB and hepatic steatosis where the comparators were: The persons in the exercise intervention group and the “do-as-usual” controls. Since no previous clinical trials have investigated the effects of aerobic exercise training in persons with CHB, we found it meaningful to use non-exercising comparators to get an estimation of the pure effects of exercise.

### Intervention description {11a}

The intervention description below follows the Consensus on Exercise Reporting Template (CERT) [49].

#### The exercise and equipment

The exercise intervention group will undergo a supervised exercise program. The exercise program includes three weekly supervised aerobic exercise training sessions of 40 min per session over 12 weeks. The program consists of high-intensity interval training on ergometer bicycles from TechnoGym (Pedan A/S, Copenhagen, Denmark) and Monark (Monark Exercise AB, Denmark) which allow monitoring and adjustment of watt. The training consists of a warm-up of 10 min, where the first 5 min are at 60–69% maximum heart rate (HR_max_) then additional 5 min at 70–79% HR_max_, followed by 25 min of high-intensity interval training, and finally a 5 min cool-down. The high-intensity interval training will be done by 4 × 4 using intervals lasting 4 min performed 4 times with 3 min restitution in between. Previous studies in CFAS have had significant results following this training program [50, 51]. The maximal oxygen consumption rate (VO2_max_) will be performed pre- and post-exercise/no-exercise intervention and will determine the relative workload accordingly. To ensure proper intensity, all patients will be wearing a heart rate monitor (Polar heart rate monitors and physical fitness watches). Since there is a good correlation between VO2_max_ and HR_max_ [52], this is a practical method to monitor the internal training load. The maximal heart rate (HR_max_) will be measured as the peak heart rate during the final minute of the VO2_max_ test [53]. Heart rate monitoring is one of the most used methods to monitor internal training load [54]. The exercise program follows the current ACSM guidelines for exercise [55] and is chosen because the exercise of similar intensity and duration is known to result in IL-6 release [55, 56] and lead to changes in VAT [55, 57].

#### Qualifications of instructors

All training sessions will be supervised and administered by CFAS personnel (students of sports science, physiotherapy students, or medical students). All CFAS personnel have attended a training session, and at least 2 supervised sessions by experienced trainers, before supervising the sessions alone.

#### Individual and small group sessions

The training sessions will mostly be performed in an individual setting, but up to 4 participants can be trained at the same time, each participant with different startup times in order to be supervised by the CFAS personnel.

#### Supervision

The supervision of the aerobic exercise training will be done by the CFAS personnel, who will physically stand next to the participant throughout the exercise session, checking the heart rate of the participant and the watts on the ergometer bike. According to the participants’ wishes, the CFAS personnel will encourage and assist with adjustment of the bike and intensity of the exercise and observe the participant when exercising.

#### Adherence to intervention and fidelity

To evaluate the precise amount of exercise completed for every patient, each training session will be documented (attendance, total time of HR_max_ > 85%, total time of exercise, average wattage, and average heart rate). The Borg Rating of Perceived Exertion scale of 6–20 [58] is used to assess the intensity of the exercise training session perceived by the participant.

#### Motivation strategies

At each exercise training session, the participant is encouraged to perform as well as possible and is complemented on their achievements and progressions during the intervention period. If there is more than one cancellation of exercise training sessions, a motivational call will be made by the primary investigator to identify complications and challenges.

#### Exercise progression

As the intervals follow the HR_max_, the watt intensity will progress throughout the 12 weeks of training.

#### Additional components

There are no home program components or non-exercise components in this trial. To control factors that may influence the intervention’s effect, the participants are instructed not to change their lifestyle habits throughout the intervention.

#### Adverse events

These will be reported at each training session.

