#### Setting

The exercise training sessions will be carried out at the facilities at CFAS and at the Department of Physical and Occupational Therapy, Copenhagen University Hospital, Hvidovre.

The participants in the control group are instructed to continue their life unchanged and will receive a standard of care in the healthcare system. Standard of care or usual care includes yearly or half-yearly visits to the Department of Infectious Diseases for control of their chronic viral disease with blood tests, fibroscan, and consultation with doctors and nurses. Also, any other treatment participants receive for any other chronic or acute disease at their general practitioner or outpatient clinic. No diet or exercise intervention is offered to the control group.

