## Data collection and management

### Plans for assessment and collection of outcomes {18a}

Most outcomes are collected at baseline, at 13 weeks follow-up, and 1 year after the intervention. Apart from these additional outcomes for physical activity, measurements assessed by accelerometers are collected at baseline, at 6 weeks, at 13 weeks, 6 months after the intervention, and 1 year after the intervention. Data collecting regarding the exercise training sessions are collected at each session and kept in a file where it will be uploaded each week.

All data will be saved in an Easytrial database where data is validated by having 2 individual persons enter data (double entry) and the database will check for inconsistency.

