### Adverse event reporting and harms {22}

Adverse events and any serious adverse events are collected during the trial; any incidents are reported back to the principal investigator immediately and noted in a separate adverse events document. The primary investigator is responsible for handling the adverse event and referring the patients to relevant departments/clinicians/insurance if needed.

Any serious incidents and adverse events (SAE) will be reported immediately to the Danish Ethical Committee. Once a year during the entire trial period, the committee system must have sent a list of all SAE and serious incidents that occurred during the period. The list must be accompanied by 1–2 pages with a summary and assessment of the subjects’ safety. All patients will be covered by The Danish Patient Insurance Association for any injury that may occur as a direct consequence of trial-related procedures.

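### Adverse event reporting is tied to training sessions that only the exercise arm attends, with no common time point for both arms, so non-serious events risk being detected unequally

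*Protocol article*

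**What the plan says.** Two places in the protocol article deal with collecting adverse events.

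- **Intervention description {11a}, Adverse events.** The whole item reads: "These will be reported at each training session".
- **Adverse event reporting and harms {22}.** "Adverse events and any serious adverse events are collected during the trial"; further, "any incidents are reported back to the principal investigator immediately and noted in a separate adverse events document". This section is not limited to one arm. It gives no time points and no method of enquiry.

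The contacts in each arm are described elsewhere.

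- **Exercise arm** (The exercise and equipment): "three weekly supervised aerobic exercise training sessions of 40 min per session over 12 weeks".
- **Control arm** (Setting): "The participants in the control group are instructed to continue their life unchanged", and "No diet or exercise intervention is offered to the control group". On routine care: "Standard of care or usual care includes yearly or half-yearly visits to the Department of Infectious Diseases".
- **Time points not limited to one arm** (Plans for assessment and collection of outcomes {18a}): most outcomes are taken at baseline, week 13 and one year. For activity monitoring, "measurements assessed by accelerometers are collected at baseline, at 6 weeks, at 13 weeks", with later points at 6 months and one year. The section does not say that adverse events are asked about at any of these.

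Trial design {8} describes the trial as unblinded, with 15 participants per arm.

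**The concern.** How many non-serious events a trial records depends on how often, and in what way, participants are given the chance to report them. Here the one concrete occasion in the text exists in one arm only. The general harms section tells staff what to do with an event once it is known, but not how events in controls come to be known between baseline and week 13.

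If the text is followed as written, a small excess of minor events among exercisers could reflect exercise, or simply more opportunities to report. The two could not be separated. The direction is against the intervention, so exercise might look less well tolerated than it is.

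This matters for use of the results. The Discussion looks ahead to offering exercise systematically in the clinic, and that needs a readable account of harms. No data monitoring committee was formed {21a}, so routine event collection is the main source of that account.

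**Working it through.** The document states no figure for adverse events, so there is none to reproduce. The check is a count of stated reporting occasions from randomization to week 13, followed by an illustration under labelled assumptions.

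**1. Stated reporting occasions**

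| Arm | Source | Count |
|---|---|---|
| Exercise | The exercise and equipment: 3 per week × 12 weeks; {11b} also gives 36 | 3 × 12 = 36 |
| Control | Setting: no exercise intervention offered | 0 |

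A participant who only just meets the attendance part of the compliance rule in {11b} completes at least 0.70 × 36 = 25.2, that is 26 sessions. The contrast is then still 26 against 0.

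**2. Does section {22} restore the balance?** It applies to both arms, so controls do have a route for reporting. It is a routing rule, however: report at once to the principal investigator and enter in a separate record. Reading {22} together with the session rule gives a general channel for both arms plus a session channel for one.

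**3. Other contacts before week 13.** Exercisers have a trainer beside them throughout each session (Supervision). They may also be contacted by the primary investigator after missed or non-compliant sessions (Motivation strategies; {11c}), and that investigator also handles adverse events under {22}. Controls have routine clinic visits once or twice a year, so many would have none in a 13-week window. Common to both arms are the week 13 assessment and a week 6 accelerometer measurement. Section {18a} does not say whether week 6 involves a visit or conversation.

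**4. Which events are affected?** Non-serious, self-reported events are exposed. Serious events depend less on contact frequency. ALT, AST, INR, FIB-4, viral load and fibroscan are scheduled at week 13 without restriction by arm (Outcomes {12}).

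**5. Illustration (assumed inputs, not from the document).** If the true risk p is the same in both arms and s is the probability that an event is recorded, the observed risk is p × s. The apparent risk ratio is then s(exercise) / s(control). Take p = 0.40, 15 per arm and s(exercise) = 0.95:

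| s(control) | Risk ratio | Expected participants with a recorded event, exercise vs control |
|---|---|---|
| 0.95 (equal) | 0.95/0.95 = 1.00 | 5.7 vs 5.7 |
| 0.80 | 0.95/0.80 = 1.19 | 5.7 vs 4.8 |
| 0.60 | 0.95/0.60 = 1.58 | 5.7 vs 3.6 |
| 0.40 | 0.95/0.40 = 2.375 | 5.7 vs 2.4 |

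The first number is 15 × 0.40 × 0.95 = 5.7; the control numbers are 15 × 0.40 × s(control). The ratio only returns the chosen detection probabilities, so this shows direction and mechanism and is not an estimate. With 15 per arm, a difference of one to three participants is enough to change the picture.

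**The case against.** The strongest reply is that the session sentence is not the harms plan. It belongs to an intervention description that follows an exercise-reporting template, and it says how events around training are recorded. The harms plan is {22}, which covers the whole trial and both arms. The article condenses a fuller protocol, which may hold an event schedule and question wording. The sentence also says events are reported, not that participants are asked. Finally, adverse events are not among the outcomes in {12}, and {20a} plans no between-arm harms analysis.

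Much of this stands. Section {22} is a real second channel, and the absence of a control-arm schedule from the article does not show that none exists. If {22} were carried out with equal intensity in both arms, the ratio above would be 1.00.

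The reply does not remove the point, because the point rests on what the article does state: an arm-specific reporting occasion beside a general sentence that does not offset it. The lack of a planned test is only partial protection. The trial commits to CONSORT-extension reporting {8}, and listing events by arm invites comparison whether or not a test is run.

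A reader might go further in three ways that the document does not support.

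- **That every between-arm safety statement is biased.** Serious events depend little on contact frequency, and events gathered at common time points can be compared.
- **That the ratio of asking occasions is 38 to 2, or 19 to 1.** This counts weeks 6 and 13 as enquiries in both arms, which the text does not say. The supported count is 36 to 0, and a ratio of contacts is not a ratio of detection.
- **That liver-related harm in controls will be missed.** The liver measurements at week 13 are scheduled without restriction by arm.

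**Conclusion.** The point holds as a risk of unequal ascertainment, confined mainly to non-serious events. Its documented size is 36 stated reporting occasions in the exercise arm against none in the control arm up to week 13, in an unblinded trial with 15 per arm. No size for the resulting bias can be taken from the document; the ratios of 1.19 to 2.375 follow entirely from assumed detection probabilities.

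The conclusion assumes that staff follow the text as written and that no common enquiry is fixed elsewhere. If the full protocol already fixes one, the article needs only to say so. The primary outcome, an MRI measurement, is untouched. A correction is worth making because it is cheap and improves how harms can be read.

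**What to change.** In the Adverse events item of {11a} and in {22}:

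1. Ask the same structured, non-leading adverse event question in both arms at the existing week 13 assessment, and at the week 6 accelerometer time point if it involves contact with the participant.
2. Base any between-arm harms table on these common-time-point answers plus all serious adverse events.
3. Report events raised at training sessions as a separate listing, labelled as exercise arm only.

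Immediate reporting under {22} stays as it is in both arms.

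The cost is one short form per common contact and a sentence in each of the two sections, submitted as an amendment under {25}. The by-arm table will leave out events reported only at sessions, and this is why the separate listing is needed. The change narrows the imbalance without abolishing it: exercisers used to reporting at sessions may still recall more at week 13. As 13 participants had been recruited by January 2023 (Trial status), anyone already past week 13 will lack the common question, and the report should give the number asked in each arm.
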